*General Practitioner Education:* All GPs in the six study areas assigned to this intervention were invited for training, with the realistic aim to train at least two-thirds of all GPs from each area. The training of community GPs instead of specialised physicians was again to ensure a sustainable programme. The training was a one day session focused on standard treatment for the management of hypertension, based on the seventh report of the Joint National Committee (JNC 7) and the Fourth Working Party of the British Hypertension Society guidelines modified for the Indo-Asian population.[18](#_ENREF_18),[19](#_ENREF_19),[3](#_ENREF_3) Components of the course included non-pharmacological (diet, exercise, weight loss, smoking cessation) and pharmacological interventions; prescribing low cost and appropriate generic drugs; preferential use of single dose drug regimens; scheduled follow-up visits guided by level of BP; stepped care approach for titration of drugs to achieve target BP levels; and satisfactory consultation sessions for patients, with explanations of treatment and use of appropriate communication strategies.

Study Diagram

12 Clusters

n = (7,166)

Total aged 40 years and over n = (3143),

Total aged 15-39 years n = (2348),

Total aged 5-14 years n = (1675)

Household Health Education (HHE) n = (1313)

Aged 40 years and over n = (1,632),

Aged 15-39 years n = (1,175),

aged 5-14 years n = (833)

(Height, Weight, Blood Pressure, Waist Hip ratio,

Food Frequency Questionnaire, Tobacco,

Physical Activity)

Age > 40 years n = (1,511)

((FPS, lipids, ACR, ECG) ECG)

)

Ineligible for other components of the study

Age > 40 years n = (1,632)

(FPS, lipids, ACR, ECG)

Age > 40 years

with hypertension

n = 680

(FBS, lipids, ACR, ECG, Echo)

)

Usual Care

Hypertension Management

Special Care

Hypertension Management

6 Clusters

6 Clusters

Usual Care

Hypertension Management

Special Care

Hypertension Management

n = 348

n = 332

n = 326

n = 335

+ HTN

+ HTN

No HTN

No HTN

Age < 40 years

No Household Health Education (HHE) n = (1337)

Aged 40 years and over n = (1,511),

aged 15-39 years n = (1,173),

aged 5-14 years n = (842)

(Height, Weight, Blood Pressure, Waist Hip ratio,

Food Frequency Questionnaire, Tobacco,

Physical Activity)

Age > 40 years

with hypertension

n = 661

((FBS, lipids, ACR, ECG, Echo)

HTN=hypertension, FBS= fasting blood sugar, ACR= urine albumin to creatinine ratio, Echo=Echocardiography

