### Rationale for assessing clinical cardiovascular risk factors

High blood glucose and high serum cholesterol are established modifiable risk factors for CVD, and confer a high attributable burden to mortality in low and middle income countries. [32](#_ENREF_32)[1](#_ENREF_1) Both types of interventions delivered during the COBRA trial included an emphasis on health related behaviour, which have been shown to improve glycemic status and lipid profiles in other studies. [25](#_ENREF_25)[33](#_ENREF_33) About 28% of hypertensive subjects in COBRA had diabetes (fasting blood sugar ≥ 7.0 mmol/L (126 mg/dL) or on antidiabetic medication), and 39% had hyperlipidemia (fasting serum cholesterol of ≥ 5.18 mmol/L (≥200 mg/dL)). Evidence on the relationship between albuminuria and CVD is accumulating. [34](#_ENREF_34) Lifestyle interventions have been shown to reduce albuminuria, and [35](#_ENREF_35) studies also indicate that risk of CVD associated with albuminuria may be modifiable. [36](#_ENREF_36) Therefore, we plan to obtain a fresh blood and urine sample for measurement of these risk factors. The assessment of change in plasma glucose, serum cholesterol and albuminuria from baseline to post trial follow-up by randomized group will provide useful information on a broad range of impact of interventions- which probably extend beyond just BP lowering. The findings will also provide mechanistic clues on any benefit of their role in the reduction of CVD morbidity and mortality in our study.

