# METHODS

All participants in the trial (originally aged 5 and now 13 years or over) will be visited by trained field staff masked to randomization status. However, the individuals (children or individuals aged 15 – 39 years) not enrolled in the main study, pregnant women, bed ridden and/or mentally retarded study subjects unable to consent will be excluded. Eligibile subjects will be offered informed consent. The date and time for interview will be set at individual’s convenience after obtaining informed consent. Information on socioeconomic status assessed via household possessions and income, occupation and literacy status, diet, physical activity (modified IPAQ), and tobacco use would be collected and weight, height, waist and hip circumference would be measured. In addition, questionnaires on health related quality of life (SF-36 and EQ-5D) will be administered to all subjects aged 40 and over with hypertension after translation in Urdu and pre-testing. As collected during baseline, the names and doses of current anti-hypertensive medications will be recorded.

As during the COBRA trial, BP will be measured with a calibrated automated device, Omron HEM-737TM Intellisense BP Monitor, in the sitting position after 5 minutes of rest using an appropriate sized paediatric or adult cuff, as applicable.[51](#_ENREF_51) BP measurements will be repeated after two weeks. Three consecutive readings will be taken at each visit, and the mean of the final two used in the analysis. The visits will be balanced across the four randomised groups and planned during the first half of the day to minimise seasonal and diurnal variation in measurements, respectively. Maximum three visits will be paid for those not present at a scheduled date and thereafter, they will be labelled as lost to follow-up.

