## Ancillary Study- Survey of General Practitioners:

The data collectors masked to randomization status will approach all GPs practicing in the 12 randomized clusters to administer a standardized questionnaire. It will contain questions on six basic themes: a) type of practice: average number of patients seen, b) information about the GP: gender, years into practice, c) detection of high BP: whether BP is measured on all or all new patients, how many readings and when, criteria for diagnosing high BP, and whether these criteria differ for the elderly as opposed to young adults, d) evaluation of patients with high BP: whether laboratory investigations for coexisting conditions (diabetes, hyperlipidemia, kidney failure) are obtained on hypertensive patients, e) management of hypertension: patient education regarding deleterious effects of hypertension, advice on non-pharmacological measures to control hypertension, the level of BP that is targeted during treatment, and choice of antihypertensive medications, and f) types of antihypertensives used (generic or branded), g) whether antihypertensives are discontinued once BP is controlled.

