## Outcome Measures

*Primary:*

In all subjects:

- Change in systolic BP from baseline to mean of two post trial follow-up visits.
- Composite of CVD morbid events and all-cause mortality.

*Secondary:*

In all subjects:

- Change from baseline to post trial follow-up in the following: body mass index (BMI), waist hip ratio, current tobacco use, total physical activity, and dietary intake of fruit and vegetables.

In the high risk cohort

- Percent change in plasma glucose (and incident pre-diabetes or diabetes defined as (fasting plasma glucose 100 mg/dl (5.5mmol/L) or more or initiation of hypoglycaemic agent)[58](#_ENREF_58), total and LDL cholesterol (and incident hyperlipidemia defined as total serum cholesterol >=200 mg/dl (5.18 mmol/L); LDL cholesterol >=130 mg/dl (3.37mmol/L))[59](#_ENREF_59), albumin excretion rate (and incident albuminuria defined as spot urine albumin to creatinine ratio of 30mg/g or greater)[60](#_ENREF_60) , and estimated glomerular filtration rate from baseline to post trial follow-up;
- Left ventricular mass index and E/A’ ratio at post trial follow-up.[39](#_ENREF_39),[61](#_ENREF_61)

Ancillary:

In the high risk cohort

- Overall mean score on Patient Health Related Quality of Life (HRQOL) based on 36-Item Short-Form Survey.

Data Collection and Management

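### Incident hyperlipidaemia is defined by lipid values alone, while the glucose outcome in the same bullet also counts drug initiation, so new cases treated to below the cut-offs are recorded as non-cases

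*Protocol*

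**What the plan says.** Protocol section 2.4 (Outcome Measures) lists percent changes in glucose, lipids and albumin excretion for the high-risk cohort and adds an incident-disease outcome in brackets after each. For glucose the case definition is "fasting plasma glucose 100 mg/dl (5.5mmol/L) or more or initiation of hypoglycaemic agent". For lipids it is "incident hyperlipidemia defined as total serum cholesterol >=200 mg/dl (5.18 mmol/L); LDL cholesterol >=130 mg/dl (3.37mmol/L", and nothing about treatment follows.

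Section 1.3.3, on clinical risk factors, shows the same difference at baseline. Diabetes there is "fasting blood sugar ≥ 7.0 mmol/L (126 mg/dL) or on antidiabetic medication". For lipids the protocol reports that "39% had hyperlipidemia (fasting serum cholesterol of ≥ 5.18 mmol/L (≥200 mg/dL", again by value alone.

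On drug data, section 2 (Methods) says that "the names and doses of current anti-hypertensive medications will be recorded". Section 2.4.4 names Form A as the questionnaire for those aged 40 and over but does not show its items. Section 3.1 allows models that account for lipid levels. It does not mention lipid-lowering treatment.

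**The concern.** Treatment can hide a new case from a laboratory threshold. The glucose definition deals with this by counting drug initiation; the lipid definition does not. Someone whose cholesterol rose above the cut-off, who was treated, and who is below it when the follow-up sample is drawn has had incident hyperlipidaemia, but the plan counts that person as never having had it.

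The same gap at baseline lets a person already controlled on a lipid-lowering drug enter the at-risk set as free of the condition.

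The certain consequence is an undercount. The further risk concerns interpretation. If one randomised group has more of its new cases detected and controlled, that group will show lower incidence, and the result could be read as prevention when only treatment differed. For percent change in cholesterol, a treated value can be defended as part of the intervention's effect. For incident disease that defence is much weaker.

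**Working it through.** The protocol states no incidence, power or treatment rate for this outcome, so there is no figure of its own to reproduce. The check has two parts.

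**Text.** The two case definitions differ as follows.

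| | Value criterion | Drug criterion |
|---|---|---|
| Glucose, baseline (1.3.3) | yes | yes |
| Glucose, incident (2.4) | yes | yes |
| Lipids, baseline (1.3.3) | yes | none |
| Lipids, incident (2.4) | yes | none |

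No other section supplies a lipid-drug criterion.

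**Size, on assumed inputs.** Let *I* be the true incidence, the same in both groups; *t* the share of new cases treated; and *c* the share of treated cases below the cut-offs at follow-up. Then

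observed incidence = *I* × (1 − *t* × *c*).

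None of the three is in the protocol. I assume *I* = 30% and *c* = 70% and vary *t*. The calculation applies to any two groups, with group A the one where more cases are treated.

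| *t*, A vs B | Observed A | Observed B | Risk ratio |
|---|---|---|---|
| 20% vs 20% | 0.30 × (1 − 0.14) = 25.8% | 25.8% | 1.00 |
| 10% vs 5% | 0.30 × (1 − 0.07) = 27.9% | 0.30 × (1 − 0.035) = 28.95% | 0.96 |
| 30% vs 15% | 0.30 × (1 − 0.21) = 23.7% | 0.30 × (1 − 0.105) = 26.85% | 0.88 |
| 40% vs 20% | 0.30 × (1 − 0.28) = 21.6% | 0.30 × (1 − 0.14) = 25.8% | 0.84 |

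*I* cancels from the ratio, so only *t* and *c* matter. The undercount within a group is *t* × *c* of its true cases: 3.5% of them at *t* = 5% and 28% at *t* = 40%.

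**After the change.** If drug initiation counts as a case and drugs are started only in people with high lipids, every treated case is recovered and the ratio returns to 1.00. If drugs are also started in people without high lipids, those starts become false cases. With a true incidence of 30% in both groups:

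- starts in 5% vs 2.5% of non-cases: 0.30 + 0.70 × 0.05 = 33.5% against 0.30 + 0.70 × 0.025 = 31.75%, ratio 1.06;
- starts in 10% vs 5% of non-cases: 37.0% against 33.5%, ratio 1.10.

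The amended definition can therefore err in the opposite direction, which is why both definitions should be reported.

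**The case against.** Several points on the other side have force.

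- **Not every treated case is lost.** A treated participant still above a cut-off at follow-up is counted correctly. Only those brought below it disappear. This stands, and the point is worded accordingly.
- **A difference between groups is not shown.** A reader might infer a bias in favour of the trained-GP groups. The protocol does not support that. Of the GP training it says: "The training was a one day session focused on standard treatment for the management of hypertension". The listed content includes no lipid-lowering prescribing. The GP survey will ask "whether laboratory investigations for coexisting conditions (diabetes, hyperlipidemia, kidney failure) are obtained on hypertensive patients", so detection by GPs is of interest to the investigators, but no difference by group is reported. A difference remains plausible, no more.
- **The ratios rest on assumptions.** This is correct. They also should not be read as a pooled trained-GP against usual-care result, because section 3.1 plans only a four-way comparison in the high-risk group.
- **Drug recording may be adequate.** A reader might infer from Methods that only antihypertensives are captured. That list cannot be complete: the baseline diabetes definition uses antidiabetic medication and the incident definition needs hypoglycaemic initiation. Whether lipid-lowering drugs are recorded is unknown, not known to be missing.
- **A value-only definition is a defensible choice.** It matches the baseline lipid definition, and incident albuminuria in the same bullet is also laboratory-only. But consistency with the baseline does not recover a treated case, and the protocol does accept a drug criterion for glucose.

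**Conclusion.** The point holds as a minor defect in how a secondary outcome is defined. The protocol itself fixes the definition, so this is not a detail left open for the analysis plan. As written, a new case treated to below the cut-offs is counted as free of hyperlipidaemia, and incidence is undercounted by the share of cases so treated.

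Bias in the group comparison is conditional. It arises only if that share differs between randomised groups, which the protocol neither shows nor rules out. On the assumed inputs above, the false risk ratio runs from 1.00 with equal treatment shares to about 0.84 with 40% against 20% treated and 70% of those below the cut-offs. A claim of established systematic bias would go beyond the document. Blood pressure and the composite of cardiovascular events and death do not use this definition, so the primary conclusions are unaffected.

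**What to change.** In section 2.4, extend the incident hyperlipidaemia definition with *or initiation of a lipid-lowering agent*, matching the glucose rule. Exclude known baseline users of such drugs from the at-risk set where baseline drug data exist. Before fieldwork, confirm that Form A records current lipid-lowering drugs, and add the item if it does not; use that is not asked about at the visit is hard to recover later. Report the lipid-value-only definition as a sensitivity analysis.

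The cost is one phrase, at most one questionnaire item and one additional analysis. The drawback is that drug starts for reasons other than high lipids will count as cases and could push the ratio above 1. Reporting the two definitions side by side shows whether the conclusion depends on that choice.

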Since one of the main aims the post-trial follow-up is to track the cohort for morbidity and mortality, a special field team will be dedicated to tracking those who were lost to follow-up during the initial 2 years or have relocated within the city of Karachi. We expect to recapture about 15% of those lost to follow-up with the assistance of neighbours, family members and community leaders residing in the study clusters. As Karachi is considered the business and economic hub of Pakistan with an annual population growth rate of 5%, the rate of out-migration is expected to be very low.[52](#_ENREF_52),[53](#_ENREF_53) Details of current residential address will be recorded for the possibility of shifting into another randomised cluster, although the chances are minimal as they represent 12 out of 5000 (0.24%) geographical communities in Karachi.

In all subjects in the high risk cohort (aged 40 years and above with hypertension), fasting blood sample will be collected for plasma glucose (Synchron Cx-7/Delta, Beckman, US) and lipid profile (Hitachi-912, Roche Japan). A fresh morning urine sample will also be collected for albumin (measured using nephelometry by the Array Systems method on a Beckman Coulter) and urine creatinine (Synchron Cx-7/Delta, Beckman, US). For external quality control on albumin measurements, AKUH laboratory routinely sends samples to Bio-Rad Laboratories Inc, Irvine, CA. Sera and urine samples will be stored at -70 freezer for possible future analysis.

A trained sonographer (gender-specific as culturally appropriate) will perform 2-D echocardiogram with a portable device for measurement of left ventricular mass and function (see 3.1.1). All assessments will be performed to a standard protocol that conforms to international standards for definitions and measurements.

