Doppler imaging: Transmitral Doppler inflow signals will be acquired and peak early diastolic velocity (E), peak late diastolic velocity (A), the E/A ratio, pulmonary vein, mitral valve deceleration time (DT), isovolumic relaxation time (IVRT) will be measured. In addition, Tissue Doppler imaging (TDI) of mitral valve annulus in the 4 chamber view at the septal and lateral walls will be performed as per guidelines of the American Society of Echocardiography, from which peak early (E’ or Ea) and peak late (A’ or Aa) diastolic mitral annular velocities will be measured.[55](#_ENREF_55) The E/E’ ratio, will be computed as a reflection of left atrial pressure as a measure of left ventricular diastolic function.[56](#_ENREF_56) In addition, patients will be categorized into grades of left ventricular diastolic dysfunction (none, grades I, II and III) based on established criteria.[56](#_ENREF_56) A subset of 100 subjects, stratified by sex, will be invited for a repeat measurement within one month to assess reproducibility (limits of agreement/coefficient of variation for test-re-test repeatability of LVMI and tissue Doppler parameters. Intra-observer variation in archived measurements from the same day will also be reported).[57](#_ENREF_57)

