## Primary & Secondary Outcomes:

For the main intention to treat analysis, the mean estimated value in each cluster for those with missing values at the final visit will be computed for all individuals with available measurements, and assigned to those with missing last follow-up measurements for individuals by cluster. This method of imputation of missing values has been shown to yield valid inferences and is recommended for large community intervention trials with small size clusters.[63](#_ENREF_63),[64](#_ENREF_64) The primary and secondary outcomes will be compared between randomised clusters using a nested mixed factorial design analysis of variance. Due to previously detected significant interaction between treatment assignments on BP in the high risk group, only four-way analysis will be performed in that group.[65](#_ENREF_65) A p value of <0.05 was considered to be statistically significant for the main effects. We will report the means and 95% confidence intervals for the treatment effects, adjusted for sex, age and baseline BP in the models. In addition, models will also be constructed after accounting for the baseline and post-trial measurement of fasting plasma glucose, and lipids (as indicated). In the model for CVD morbidity and mortality, albuminuria, LVMI, and E/E’ ratio we will also adjust for change in systolic BP from baseline to follow-up. The marginal adjusted probabilities will be used to calculate the risk ratios, and their 95% CI will be computed by the bootstrapping method.[66](#_ENREF_66)

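### Laboratory and echo secondary outcomes: eGFR has no planned assay, the diastolic index differs between sections, and the main model omits each analyte's own baseline

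*Protocol*

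**What the plan says.** Outcome Measures (Protocol 2.4) gives two kinds of secondary outcome for the high-risk cohort. The laboratory group opens with "Percent change in plasma glucose (and incident pre-diabetes or diabetes defined as" and goes on to total and LDL cholesterol, then "albumin excretion rate (and incident albuminuria defined as spot urine albumin to creatinine ratio of 30mg/g or greater", and closes with "and estimated glomerular filtration rate from baseline to post trial follow-up". The echocardiographic group is "Left ventricular mass index and E/A’ ratio at post trial follow-up".

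METHODS (Protocol 2) states the assays: a "fasting blood sample will be collected for plasma glucose (Synchron Cx-7/Delta, Beckman, US) and lipid profile (Hitachi-912, Roche Japan", plus one fresh morning urine sample for albumin and urine creatinine. Serum is frozen for possible later use, with no assay committed.

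The section on left ventricular mass and diastolic dysfunction (2.1) says that E/E' "will be computed as a reflection of left atrial pressure as a measure of left ventricular diastolic function".

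The analysis section for primary and secondary outcomes (3.1) reports means and confidence intervals "adjusted for sex, age and baseline BP in the models". It then plans further models that include baseline and post-trial glucose and lipids where indicated, and names E/E' among the outcomes also adjusted for change in systolic BP.

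**The concern.** An outcome list should match what is measured and what is analysed, and this one departs from both. If eGFR has no filtration marker behind it, a listed outcome will go unreported or will need an assay that nobody has planned. If the diastolic outcome has one name in the list and another in the analysis, a reader of the results cannot tell which index was prespecified.

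The covariate set is a separate matter. Baseline BP is the natural covariate for the BP outcome, but it is a poor stand-in for baseline glucose, cholesterol or ACR. Leaving out the analyte's own baseline gives up precision. It also leaves the comparison exposed to chance baseline differences between a small number of clusters.

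**Working it through.** The protocol gives no sample size, variance or correlation for these outcomes, so there is no figure to reproduce. The check sets the sections side by side and then uses algebra.

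**1. eGFR**
- Listed: percent change from baseline (2.4).
- Follow-up assays: glucose, lipids, urine albumin, urine creatinine (METHODS). No serum creatinine or other filtration marker.
- Baseline panel for hypertensive adults: fasting sugar, lipids, ACR, ECG, echo (Study Diagram, 1.2.2). No serum creatinine.
- Elsewhere: eGFR is absent from the clinical risk factor rationale (1.3.3), the aims (1.4), the hypotheses (1.5), the analysis plan (3.1) and the list of conditions participants are tested for (3.3).
- Result: a percent change needs two values, and the protocol documents neither.

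**2. Diastolic index**
- 2.4 names E/A'.
- 2.1 lists transmitral E/A and defines E/E'.
- 3.1 and the ancillary BP-variability models (3.2) analyse E/E'.
- Result: E/A' appears once and is never defined or analysed. E and A' are both recorded, so the ratio could be calculated. The fault is inconsistency, not missing data.

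**3. Albumin**
- 2.4 says excretion rate, but the same clause defines incident albuminuria by spot ACR.
- METHODS describes one untimed sample assayed for albumin and creatinine.
- Result: ACR is available and a rate is not. The name is wrong, but the outcome can be delivered.

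**4. Covariates**

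Let B and F be an analyte's baseline and follow-up values, and P = 100(F/B − 1).
- The main model for P has sex, age and baseline BP. B is absent.
- Suppose the arms differ by d in mean log B, and the within-arm slope of log F on log B is β. With no treatment effect, the expected difference in log F − log B is βd − d = (β − 1)d. This is not zero unless β = 1. Adjusting for BP removes only the part of d that BP predicts.
- With log B in the model that term is removed. Regressing log F or log(F/B) on log B gives the same treatment coefficient, so the relative-change interpretation is kept and the exponentiated coefficient is a ratio of geometric means.
- Percent change is asymmetric: a doubling is +100% and a halving is −50%. Their mean is (100 − 50)/2 = +25%, although the geometric mean ratio is √(2 × 0.5) = 1.
- The additional models bring in baseline glucose and lipids only together with F. For a glucose or lipid outcome, log(F/B) is then fully determined by the covariates and the treatment coefficient is zero by construction. On the percent scale only lack of linear fit is left to estimate it.
- No model names baseline albuminuria.
- The Study Diagram shows baseline glucose, lipids and ACR, so these covariates exist. The earlier trial's table for children and young adults (1.2.3) adjusted systolic BP for baseline systolic BP and diastolic BP for baseline diastolic BP, which is the practice recommended here.
- There are 12 clusters and the high-risk group is analysed four ways, so 12/4 = 3 clusters per group on average. Chance differences in baseline means are a practical issue at that number.

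**The case against.** The strongest reply is that outcome-specific covariates and transformations are usually left to a statistical analysis plan, and that percent change in a randomised comparison is inefficient but not invalid. The second part stands: no bias in expectation is claimed, and a skewed percent change shifts the mean in every arm without distorting the contrast between arms. The first part stands only in part. The protocol does fix one covariate set for primary and secondary outcomes together, and an analysis plan cannot supply an assay that is not performed.

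The qualifier on the additional models can also be read to mean that glucose and lipids enter only the models of other outcomes. The text allows that reading, but then no model adjusts glucose or lipids for their own baseline.

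Several stronger readings are tempting and are not supported:
- That all high-risk secondary outcomes are percent changes. LVMI and the diastolic index are post-trial values, and the incident outcomes are binary.
- That own baseline appears nowhere. Baseline glucose and lipids do enter the additional models.
- That three outcomes cannot be delivered. This applies only to eGFR.
- That the diastolic endpoint is open to choice after the data are seen. Both analysis sections name E/E', so E/A' looks like a slip.
- That a baseline for eGFR is already held. The protocol documents none.
- That a particular variance saving follows. The usual result for analysis of covariance against change scores concerns raw changes without clustering, and an individual-level saving need not carry over to a comparison of 12 clusters.

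**Conclusion.** The point holds in four parts of unequal weight. The eGFR outcome has no documented measurement at either time point, which is the most substantial mismatch. The diastolic outcome is inconsistent between the outcome list and the rest of the protocol. Albumin excretion rate is a naming error only. The main model for glucose, cholesterol and ACR omits a covariate that the trial holds and that costs nothing to include.

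The first three parts rest on the text alone, given the assays and the panel as listed. The fourth concerns precision and chance imbalance, not validity. Its size depends on baseline-to-follow-up correlations, analyte variability and clustering, none of which the protocol gives, so no figure is attached. All four parts concern secondary outcomes. The primary BP outcome is already adjusted for its own baseline.

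**What to change.** - Use E/E' as the diastolic outcome throughout, correcting the entry in Outcome Measures.
- Delete eGFR, unless a baseline serum creatinine is confirmed to exist. In that case add a follow-up creatinine assay on the stored serum and state the estimating equation.
- Replace albumin excretion rate with spot ACR.
- In the main model for glucose, total and LDL cholesterol and ACR, analyse the log follow-up value with log own baseline, age, sex and clustering. Report geometric mean ratios with confidence intervals.
- State that no outcome is adjusted for its own post-trial value, and say which outcomes the additional glucose and lipid models apply to.

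The cost is wording and model code, plus one assay if eGFR is kept. Results will be reported as ratios and not as mean percent changes, and one listed outcome may be dropped. A follow-up assay alone would not rescue eGFR as a change from baseline.
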